### Blinding

It is difficult to blind patients as well as acupuncturists for the experience of needle manipulation with or without *deqi*. However, it is feasible to conceal the group assignments from researchers, outcome assessors, and the statistician. Researchers, the acupuncturist, outcome assessors, and the statistician are separate.

### Control

To investigate the influence of the *deqi* sensation on the long-lasting acupuncture effect, we choose acupuncture without *deqi* as the control group. In addition, to avoid the influence of a self-healing tendency, we design a wait-list group in which FD patients will not receive acupuncture treatment.

### Participants and recruitment

Based on the Rome III criteria and current academic literature, FD comprises three subtypes: postprandial distress syndrome (PDS), epigastric pain syndrome (EPS), and a subtype with overlapping PDS and EPS features [26]. Among the three subtypes, FD patients diagnosed with PDS are most common in the epidemiology [27], and no significant differences were found in the acupuncture response between FD patients in PDS and FD patients in EPS in our previous study [28]. Therefore, FD patients with PDS, or the subtype with overlapping PDS and EPS features but PDS dominating will be recruited if they match the inclusion criteria. They will be briefly introduced to this study and informed about the benefits as well as possible risks associated with needling (bleeding, hematoma, or fainting). Then, the participants will be required to fill in consent forms and are free to withdraw from the study at any time without any specific reason, penalty or loss of benefits.

All researchers responsible for screening patients will be trained using the Rome III criteria in the pretrial period. They will screen a group of participants and then compare and fix their screening results to achieve homogeneity.

### Inclusion criteria

Participants who meet each of the following criteria will be included: (1) matching the Rome III criteria on FD with subtype PDS or subtype with overlapping PDS and EPS features but PDS dominating; (2) aged between 18 and 45 years, and right handed; (3) without intake of any gastroenteric dynamic drugs in 2 weeks before enrollment; (4) not participating in any other clinical trials; and (5) having signed a written informed consent form.

### Exclusion criteria

Participants who meet one of the following criteria will be excluded: (1) FD with subtype EPS or subtype with overlapping PDS and EPS features but EPS dominating; (2) having esophagitis, gastric atrophy, or erosive gastroduodenal lesions on endoscopy, cholecystitis, gallstones; (3) having psychological problems, being unconscious, having a history of mental disorders, being unable to cooperate in outcome assessment; (4) having aggravating malignant tumors or other serious consumptive diseases, infectious, bleeding diseases, etc.; (5) having used aspirin, steroids, nonsteroidal anti-inflammatory drugs, selective serotonin-reuptake inhibitors, medication affecting gastrointestinal motility, or other drugs; (6) pregnant women, or intent to, or in, the breast-feeding period within 6 months; (7) having any contraindications to fMRI scan, such as having a cardiac pacemaker, defibrillator, metal stents, or electronic device in the body, having an intraocular metal foreign body, having claustrophobia, hyperpyrexia, etc.

### Recruitment strategies

All patients will be recruited from outpatients and inpatients of the Digestive Department of the First Teaching Hospital of Chengdu University of Traditional Chinese Medicine (TCM) and the campus of Chengdu University of TCM between January 2016 to December 2018. Patients interested in this trial will be first evaluated by physicians. If they meet the criteria and decide to participate, they will be asked to sign the informed consent. Then, they will be included in this trial for randomization.

### Interventions

The acupoints used in the study include unilateral *Zhongwan* (CV12) and bilateral *Zusanli* (ST36) (Fig. 3). The combination of CV12 and ST36 is commonly used for treating FD, and has been used in our previous studies [29].

**Fig. 3 Fig3:**
[figure not shown]
Locations of acupoints. Locations of acupoints: ST36 (*Zusanli*), on the anterior lateral side of the shank, 3 *cun* below ST35 (*Dubi*), one horizontally placed finger distance lateral to the anterior border of the tibia. CV12 (*Zhongwan*), on the anterior median line of the upper abdomen, 4 *cun* above the navel. These two acupoints have been used in our previous study by Shuai Yin et al. (Cerebral mechanism of puncturing at *He-Mu* point combination for functional dyspepsia: study protocol for a randomized controlled parallel trial. *Neural Regen Res.* 2017;12: 831–840.), so as to provide a stable acupuncture effect

Acupuncture treatment will be performed by two licensed acupuncturists with clinical experience over 3 years. The acupuncturists will be trained and take an examination before participating in this trial. The two acupuncture groups will receive 20 sessions’ treatment over a period of 4 weeks. The acupuncture treatment is performed once per day for 5 days continuously then at 2-day interval.

#### Acupuncture with the *deqi* group

After the skin has been cleaned with tincture iodine and alcohol, the sterile filiform needles (0.25 mm in diameter, 40 mm in length, Hwatuo, Suzhou, China) are inserted perpendicularly into the points for 21–26 mm. Then, the needle is twisted between 90 and 180°, lifted and thrusted in an even amplitude between 0.3 cm to 0.5 cm, 60 times to 90 times per minute. After the *deqi* response (including soreness, numbness, distention, and heaviness) is obtained, the needle will be retained in the skin for 30 min, still being manipulated every 10 min twice for 10 to 15 s.

#### Acupuncture without the *deqi* group

To avoid the *deqi* response, no needle manipulation will be performed after the perpendicular insertion.

#### Wait-list group

Patients will not receive acupuncture treatment during the study. For *deqi* it is important in achieving clinical efficacy that these patients will be treated by acupuncture with *deqi* after finishing the study.

Participants with pain, bleeding, fainting, or other severe discomforts should be discontinued from acupuncture treatment and processed immediately. During the acupuncture treatment and follow-up, all participants are usually not allowed to use FD symptomatic or emotional relief medication. But if required, participants can be permitted to receive acute stomach disorder treatment, and the type and dosage of medication used should be recorded in the case report form (CRF).

### fMRI scan

Brain images will be acquired on a 3.0-T magnetic resonance scanner (Siemens, Munich, Germany) at Huaxi Magnetic Resonance Research Center, West China Hospital of Sichuan University, Chengdu, China. The scan will be performed at three time points including: baseline, the end of the treatment, and the follow-up. During the scan, each participant is blindfold, with their ears plugged, and is required to undergo a high-resolution, three-dimensional, T1-weighted and BOLD-fMRI sequence. Three-dimensional anatomic image parameters are as follows: repetition time/echo time = 1900 ms/2.26 ms, slices = 30; matrix size =128 × 128, field of view = 256 × 256 mm^2^, slice thickness = 1 mm. The BOLD images will be acquired as: repetition time/echo time = 2000 ms/30 ms, flip angle = 90°, slices = 30; matrix size = 128 × 128 mm^2^, field of view = 240 × 240, slice thickness = 5 mm.

### Patient safety

To provide health evaluation before randomization, physical examination for participants will be conducted including gastroscope examination, abdominal ultrasound, blood biochemical test (ALT, AST, BUN, serum creatinine), and electrocardiogram examination. To assess the risks associated with acupuncture, the blood biochemical test will be completed again at the end of treatment. Adverse events, such as pain, bleeding, fainting, or other severe events, should be processed immediately and recorded in the CRF carefully.

### Outcome assessments

The following outcomes will be assessed by independent outcome assessors. These assessors are trained before participating in this trial and blinded to the randomization. Outcome data for participants either completed or discontinued during the study will be collected and recorded.

Clinical outcome assessments include: symptoms, QOL, and psychosocial state. All evaluations will be performed at three time points (the baseline, the end of 20 sessions of acupuncture and the end of follow-up, respectively) (Fig. 2).

The Nepean Dyspepsia Index (NDI) is primarily used to measure the symptoms and QOL for FD patients [30]. It includes the following two parts. The symptom checklist measures 15 upper gastrointestinal symptoms regarding frequency, intensity, and level of discomfort. The QOL checklist includes four aspects, namely life interference (13 items), knowledge/control (seven items), eating/drinking (three items), and sleep/disturbance (two items). Higher scores indicate more severe symptoms and poorer QOL. Our prior research found that the Chinese version of the NDI was reliable and valid for measuring QOL in Chinese FD patients [31].

The short form Leeds Dyspepsia Questionnaire (SF-LDQ) [32] is also performed to assess the symptom severity. The SF-LDQ is a validated and reliable tool with five questions instrument to measure the patients’ dyspeptic symptoms. Five questions are used for five symptoms including epigastric pain, postprandial distention, indigestion, heart-burn, and nausea. By using a five-point Likert scale, the symptoms are graded for severity from very mild to very severe: no symptoms (0 point), very mild symptoms without influence of regular work (1 point), mild symptoms with influence of regular work (2 points), moderate symptoms (3 points), severe symptoms (4 points), and extremely severe symptoms (5 points). The severity of dyspepsia is evaluated by total scores on these five symptoms. Higher total scores indicate more severe symptoms.

As emotional changes, such as anxiety and depression, are commonly seen accompanying symptoms in FD patient, the Zung Self-Rating Anxiety Scale (SAS) [33], the Zung Self-Rating Depression Scale (SDS) [34], the Beck Anxiety Inventory (BAI) [35], and the Beck Depression Inventory (BDI) [36] are used in this study to evaluate the psychological condition of patients.

### Needle sensation evaluations

Participants in the two acupuncture groups will be asked to fill the needle sensation evaluation form after receiving each acupuncture treatment. The form is based on the Chinese version of modified Massachusetts General Hospital Acupuncture Sensation Scale (C-MASS) [37, 38], and its validity and reliability have been examined [38, 39]. In the form, the Visual Analog Scale (VAS) [40] is selected to quantitatively evaluate the *deqi* sensation after each acupuncture treatment. This is a 10-point scale with anchor words “none” (no score), “mild” (about two scores), “moderate” (around five scores), “severe” (almost eight scores), and “unbearable” (nearly ten scores) spaced along the continuum. The scale will be used to access evaluate the *deqi* sensations (including soreness, numbness, fullness, heaviness, aching), respectively. Moreover, if the scale does not completely describe the needle sensations that subjects experienced, subjects can add what they feel in a blank row below the scale.

Since some participants were sensitive while some were not, both acupuncture groups’ participants will be re-divided into the “actual *deqi* group” and “actual without *deqi* group” according to the median of the mean needle sensation score across 20 times treatment. Then the “actual *deqi* group” and “actual without *deqi* group” will be compared with both clinical data and fMRI data.

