### Sample size

According to our previous study, Nepean Dyspepsia Index (NDI) scores of FD patients decreased by 12.2 points after acupuncture and by 7.8 points after sham acupuncture [23]. In this study, we anticipated a reduction of NDI score by 12 points after acupuncture with the *deqi* sensation and a reduction by 8 points after acupuncture without the *deqi* sensation, and we anticipated a reduction by 4 points in the wait-list control due to regression to the mean effect. With *α* = 0.05, 1 − *β* = 0.8, and a standard deviation of 10, we needed at least 96 participants in total. Considering a dropout rate of 10%, a total of 105 participants will be included in this trial. According to the sample size of previous blood-oxygenation-level-dependent fMRI (BOLD-fMRI) studies, 20 subjects is the reasonable sample size with stable statistical effect [24, 25]. Considering the dropout rate and loss of data due to head motion during fMRI scans, 25 participants from each group will receive fMRI scans in this study.

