## Data analysis

### Clinical data analysis

The intention-to-treat analysis will be used for all allocated participants in the baseline. This study focuses on the lasting-effect of acupuncture, and the observed data will be used as the primary analysis and last observation-carried-forward (LOCF) analysis will be taken as a sensitivity analysis. Clinical outcome will be analyzed using SPSS 22.0 statistics software (IBM SPSS Statistics, IBM Corp, Somers, NY, USA). Data on Skewed distribution will be normalized. Means, standard deviations, and 95% confidence intervals (CIs) will be used to describe the continuous data.

The demographic and baseline characteristics among three groups will be compared using one-way analysis of variance (ANOVA). A *χ*^2^ test will be used for categorical variables. Due to the occurrence of self-healing tendency in FD, it is important to testify the existence of acupuncture effect. The clinical outcome NDI and SF-LDQ scores will be compared between the acupuncture group and the wait-list group among three time points by using the repeated measures ANOVA (two independent groups with repeated measures). Then, the acupuncture group with and without *deqi* at three time points will be primarily compared using repeated measures model.

A two-sided test will be used during the analysis, with a significance level of 0.05. The data will be analyzed by statisticians who are blinded to the test settings.

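### The added 'actual deqi' comparison, split at the median of patients' own sensation scores, is not protected by randomisation and should be exploratory, with deqi conclusions resting on the allocated arms

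*Protocol article*

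**What the plan says.** The Needle sensation evaluations section of the protocol article has patients in both acupuncture arms rate their sensations on a 0 to 10 visual analogue scale after each session. Because some patients are sensitive and others are not, the two arms are then to be re-divided "according to the median of the mean needle sensation score across 20 times treatment". The new 'actual deqi' and 'actual without deqi' groups "will be compared with both clinical data and fMRI data". The section names no adjustment for allocated arm or baseline, and does not call the comparison secondary or exploratory.

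Four other sections bear on this:
- **Clinical data analysis** specifies intention-to-treat for all allocated participants and makes the repeated-measures comparison of the with-deqi and without-deqi groups the primary one. It adds: "A two-sided test will be used during the analysis, with a significance level of 0.05".
- **fMRI data analysis** contrasts deqi with no deqi, without saying whether the allocated or the 'actual' groups are meant.
- **Blinding** says that patients are difficult to blind.
- **Background** gives, as the third aim, the influence of deqi on the long-lasting effect and its central mechanism.

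**The concern.** The patients themselves produce the score that defines the new groups, after allocation and while knowing what is being done to them. The NDI and SF-LDQ also record patients' own symptoms. Somatic sensitivity, expectancy or response style can therefore move both the grouping variable and the outcome. The stated reason for the split, differing sensitivity, names just such an unrandomised trait.

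The cut-point adds two problems. A sample median is not a threshold for deqi: with 70 acupuncture patients it puts about 35 in each half, whatever they felt. A manipulated patient with moderate sensation can be labelled 'without deqi', and an unmanipulated patient 'actual deqi'. Splitting also throws away the grading: for a normally distributed score, a median split keeps about 2/π = 64% of the information on a linear relation.

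At stake is the third aim. A positive 'actual deqi' result could be read as an effect of deqi when it reflects who the sensitive patients are, above all for the fMRI data, where the grouping is not fixed.

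**Working it through.** **Inputs from the Sample size section.** The planned NDI reductions are 12 ("we anticipated a reduction of NDI score by 12 points after acupuncture", with deqi), 8 ("a reduction by 8 points after acupuncture without the" sensation) and 4 ("we anticipated a reduction by 4 points in the wait-list control"). Power and SD are given as "0.8, and a standard deviation of 10". Study design allocates 35 per arm.

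**Check of those inputs.** The plan states "and a standard deviation of 10, we needed at least 96 participants in total". For a three-group one-way ANOVA, f = √{[(4² + 0 + 4²)/3]/10²} = 0.3266. Power is 0.798 at N = 93 and 0.812 at N = 96, so 96 is the smallest balanced total reaching 0.80. The figure reproduces, and the inputs can be used below.

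**The randomised contrast as benchmark.** The planned difference between the acupuncture arms is 12 − 8 = 4 points. As a simple two-group comparison, its power is 0.36 at 32 per arm and 0.39 at 35 per arm (normal approximation); 80% would need 99 per arm.

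**Model for the split (assumptions, not in the documents).** Within each arm, sensation is normal with SD 1. The arms differ by S. The score correlates r with NDI reduction (SD 10) through a patient trait. τ is the true effect of allocation.

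- Share of each arm that falls in the other half: q = Φ(−S/2), which is 40%, 31% and 16% for S = 0.5, 1 and 2.
- Gap in the trait between the halves: 4φ(S/2).
- Expected difference between the halves: D = τ(1 − 2q) + 10 · r · 4φ(S/2).

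Examples: with τ = 0, S = 0.5, r = 0.3, D = 10 × 0.3 × 4 × 0.3867 = 4.64. With τ = 0, S = 2, r = 0.2, D = 10 × 0.2 × 4 × 0.2420 = 1.94. With τ = 4 and r = 0, only 4(1 − 2q) remains: 3.2, 2.4 and 1.6 points at q = 10%, 20% and 30%.

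**Simulation, 35 per arm, 20,000 trials per cell.** Each cell gives the mean difference in points and the two-sided rejection rate at 0.05 for the split groups.

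| Scenario | S = 0.5 | S = 1 | S = 2 |
|---|---|---|---|
| τ = 0, r = 0.2 | 3.04; 25% | 2.77; 21% | 1.90; 12% |
| τ = 0, r = 0.3 | 4.58; 49% | 4.15; 42% | 2.82; 22% |
| τ = 4, r = 0 | 0.81; 6% | 1.55; 10% | 2.72; 20% |
| τ = 4, r = 0.3 | 5.37; 62% | 5.70; 67% | 5.57; 65% |
| τ = 4, r = −0.2 | −2.26; 15% | −1.22; 8% | 0.86; 6% |

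In the same runs the allocated-arm test rejects in 5% of trials when τ = 0, and gives about 4.0 points with 37 to 38% rejection when τ = 4.

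**A second set, 32 per arm, S = 1 to 2.** Here the trait correlates 0.5 with sensation and 0.5 or 0.3 with outcome, so the implied r is 0.5 × 0.5 = 0.25 or 0.5 × 0.3 = 0.15. With τ = 0 the split rejects in 16 to 29% and 8 to 13% of trials respectively.

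Together, the false-positive rate runs from roughly 8% to 49%. With a true effect of 4, the split can show less than 4, more than 4, or the opposite sign.

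**The case against.** The strongest reply is that this is only an added comparison. A reader might infer that the split replaces the randomised arms. The documents do not support that: Clinical data analysis keeps intention-to-treat and names the allocated with-deqi and without-deqi groups as the primary comparison, and the regrouped sets carry separate names. For clinical data its subordinate place can be read from the text, although nothing says which result decides if the two disagree. For fMRI data no such protection is stated.

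A reader might also infer that the split necessarily dilutes a real effect. It does so when sensation has no link with outcome (table, third row), but not in general. If the whole 4 points ran linearly through sensation, the halves would differ by (4/S) × 2[2φ(S/2) + (S/2)(2Φ(S/2) − 1)]: 4 × 1.791 = 7.2 points at S = 1 and 2 × 2.333 = 4.7 at S = 2. The direction of bias depends on quantities that the documents do not give.

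The false-positive rates likewise rest on assumed correlations and separations. They illustrate a mechanism and do not size it for this trial.

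Finally, how the 20-session mean is formed for patients who stop early is commonly left to the full protocol or analysis plan, and is not counted here. The same reply does not dispose of the main point, which concerns a rule that the article states, not a detail that it omits.

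**Conclusion.** The concern stands for the added 'actual deqi' comparison. It is formed after randomisation from unblinded self-report, is cut at a data-dependent median, and by the protocol's own reasoning separates patients by sensitivity. Followed as written, it does not estimate an effect of deqi that randomisation protects, and it may be inflated, diluted or reversed. The range of roughly 8 to 49% false positives instead of 5% assumes arms 0.5 to 2 SD apart on sensation and an effective sensitivity-outcome correlation of 0.15 to 0.3; with no such correlation the rate stays at about 5%.

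The primary clinical comparison of the allocated arms is unaffected. The exposure is in interpretation: the randomised 4-point contrast has only about 36 to 39% power on the planning figures, so a null randomised result beside a positive 'actual deqi' result is realistic. The exposure is greatest for fMRI, where the grouping behind the deqi contrast is not stated.

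**What to change.** 1. State that every conclusion about deqi, clinical and fMRI, rests on the arms as randomised, and say in fMRI data analysis that the contrast uses the allocated groups.
2. Replace the median split with a model of outcome on the continuous mean sensation score, adjusted for allocated arm and the baseline value of the outcome.
3. Label that model exploratory and observational. Adjusting for arm does not remove confounding by sensitivity, so the label is needed even with the better model.

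Using allocation as an instrument for felt deqi is not a sound alternative: allocation changes the needle manipulation itself and patients are not blinded, so it can affect reported outcome by other routes.

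The cost is a change of wording and slightly more analysis work; no new data are needed. The downside is the loss of a headline 'actual deqi' group comparison.

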### Data management and monitoring

The CRFs for each participant will be prepared in both paper and electronic versions. Only outcome assessors have access to CRFs and will perform the double-data entry. The Evidence-based Medicine Center of the university will be responsible for monitoring the study as well as the data every 3 months.

## Data analysis

### Clinical data analysis

The intention-to-treat analysis will be used for all allocated participants in the baseline. This study focuses on the lasting-effect of acupuncture, and the observed data will be used as the primary analysis and last observation-carried-forward (LOCF) analysis will be taken as a sensitivity analysis. Clinical outcome will be analyzed using SPSS 22.0 statistics software (IBM SPSS Statistics, IBM Corp, Somers, NY, USA). Data on Skewed distribution will be normalized. Means, standard deviations, and 95% confidence intervals (CIs) will be used to describe the continuous data.

The demographic and baseline characteristics among three groups will be compared using one-way analysis of variance (ANOVA). A *χ*^2^ test will be used for categorical variables. Due to the occurrence of self-healing tendency in FD, it is important to testify the existence of acupuncture effect. The clinical outcome NDI and SF-LDQ scores will be compared between the acupuncture group and the wait-list group among three time points by using the repeated measures ANOVA (two independent groups with repeated measures). Then, the acupuncture group with and without *deqi* at three time points will be primarily compared using repeated measures model.

A two-sided test will be used during the analysis, with a significance level of 0.05. The data will be analyzed by statisticians who are blinded to the test settings.

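### Intention-to-treat is promised, but the wait-list comparison uses repeated measures ANOVA on observed data, and the LOCF check assumes persistence for patients lost after treatment

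*Protocol article*

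**What the plan says.** The Clinical data analysis section fixes four things.

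- Population: "The intention-to-treat analysis will be used for all allocated participants in the baseline".
- Data rule: "This study focuses on the lasting-effect of acupuncture", and in the same sentence "the observed data will be used as the primary analysis and last observation-carried-forward (LOCF) analysis will be taken as a sensitivity analysis".
- Model for acupuncture versus wait-list: NDI and SF-LDQ over three time points, compared "by using the repeated measures ANOVA (two independent groups with repeated measures").
- Model for the deqi question: "the acupuncture group with and without *deqi* at three time points will be primarily compared using repeated measures model". The type of model is not named.

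Under Outcome assessments the article adds: "Outcome data for participants either completed or discontinued during the study will be collected and recorded". The Sample size section allows for 10% dropout overall, without saying when it occurs or in which arm. The first aim, at the end of the Background, is to confirm the long-lasting effect by comparing baseline, end of treatment and end of follow-up.

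**The concern.** Two parts of this do not fit together.

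First, classical repeated measures ANOVA needs a complete set of visits for each patient. Applied to observed data it drops a patient who misses any of the three assessments, together with the scores that patient did give. For the wait-list comparison that is a complete-case analysis, not an analysis of all allocated participants. It discards partial data that the article says will be collected.

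Second, the trial is about whether benefit continues once needling stops. For a patient assessed at the end of treatment but not at follow-up, LOCF fills the gap with the end-of-treatment score, so that patient is recorded as having had no relapse. A check built on that assumption cannot challenge a claim of persistence among the patients for whom the claim is least certain.

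At stake is the first aim. A sensitivity analysis that agrees with the primary result would be read as support, although for late losses it was constructed to show persistence.

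**Working it through.** **Inputs from the Sample size section.** NDI reductions of 12 (deqi), 8 (no deqi) and 4 (wait-list), SD 10, alpha 0.05, power 0.8, 96 evaluable, 10% dropout, 105 in total.

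**The plan's own figure.** A three-group one-way F test has f = sqrt[(4² + 0² + 4²)/3]/10 = 0.327. Power is 0.798 at 31 per group and 0.812 at 32 per group, so 96 reproduces. For dropout, 96/0.9 = 106.7 and 96 × 1.1 = 105.6; 105 is close to both. The sample size is not in dispute.

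**Loss from a complete-case analysis.** 105 × 0.9 = 94.5, so about 10 of 105 patients, or 3 to 4 per arm if evenly spread, would contribute nothing to an analysis that requires all three visits.

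**LOCF, loss after end of treatment.** Let a share d of an arm be seen at end of treatment and missing at follow-up, unrelated to outcome, and let the true relapse be r. LOCF gives the missing patients a change of 0, so the arm shows (1 − d) × r + d × 0 = (1 − d)r. With r = 4 (assumed):

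- d = 5%: 0.95 × 4 = 3.8
- d = 10%: 0.90 × 4 = 3.6
- d = 20%: 0.80 × 4 = 3.2

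In levels, if improvement is 12 at end of treatment and truly 8 at follow-up, 10% late loss gives 0.9 × 8 + 0.1 × 12 = 8.4.

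**LOCF, loss before end of treatment.** Here baseline is carried forward to both later visits. With the same 12 and 8 and 10% early loss, the arm shows 0.9 × 12 = 10.8 and then 0.9 × 8 = 7.2. Follow-up benefit is understated, not overstated.

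**Between-arm difference at follow-up, deqi minus no deqi.** Simulation with 200,000 per arm, SD 10, end-of-treatment improvements of 12 and 8, a 4-point relapse in both arms, and all loss after end of treatment. The within-person correlation of 0.6, the relapse and the dropout splits are assumptions. The last column is a missing-at-random (MAR) estimate that uses the end-of-treatment score.

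| Dropout, deqi / no deqi | Dropout depends on | True | Complete cases | LOCF | MAR |
|---|---|---|---|---|---|
| 10% / 10% | end-of-treatment score | 3.94 | 3.92 | 3.93 | 3.93 |
| 10% / 10% | unseen follow-up score | 4.03 | 4.03 | 4.02 | 4.03 |
| 5% / 15% | end-of-treatment score | 4.01 | 3.51 | 3.90 | 4.03 |
| 5% / 20% | end-of-treatment score | 4.01 | 3.26 | 3.77 | 4.01 |
| 5% / 20% | unseen follow-up score | 4.02 | 2.76 | 3.05 | 3.18 |

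In this set-up each arm's bias depends only on its own dropout rate, so exchanging the two rates reverses the sign of the bias.

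**Relapse within the 20% arm.** When dropout depends on the end-of-treatment score, the true 4.01 shows as 4.69 in complete cases and 3.75 under LOCF. When it depends on the unseen follow-up score, the true 4.00 shows as 3.31 in complete cases, 2.65 under LOCF and 2.84 under the MAR estimate.

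**Unequal relapse.** With none in the deqi arm, 4 points in the other and 10% dropout in each, the true difference of 7.99 shows as 7.59 under LOCF and 7.99 in complete cases.

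**The case against.** The best defence is that the main comparison is not shown to be complete-case. The deqi contrast is assigned a repeated measures model, not ANOVA. If that means a likelihood mixed model, observed data from all allocated participants is sound and consistent with intention-to-treat. This stands: the text leaves the model open, although the sentence before it names ANOVA.

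The article also seems to have made observed data primary because persistence is the target, leaving LOCF as the check. That is the better order of the two, but it does not make LOCF an informative check.

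Collecting outcomes from patients who discontinue may keep the missing share small. That stands as mitigation; it does not change the analysis rule for scores that are still missing.

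A full analysis plan may contain further sensitivity analyses. That is why the point rests on the methods that the article fixes, and not on LOCF being the only check.

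A reader might go further and infer that both analyses overstate persistence. The documents do not support this. LOCF works against benefit for early losses, and complete cases can overstate relapse (4.69 against 4.01 above). A reader might also set the 0.4-point excess (8.4 against 8) against a 4-point difference and call it a 10% bias. That needs an assumed relapse from 12 to 8 and all dropout after treatment, and the planned gap between deqi and wait-list is 8 points, not 4.

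**Conclusion.** The concern holds in a limited form. For acupuncture versus wait-list, the stated method conflicts with the stated population. For deqi versus no deqi, the model needs to be named before one can say whether it does. LOCF assumes persistence for patients lost between end of treatment and follow-up, and no improvement for those lost earlier.

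The size is modest at the planned dropout. Late loss unrelated to outcome shrinks an arm's relapse by the share missing. The deqi versus no-deqi difference is essentially unbiased when dropout and relapse are equal across arms. It matters more if dropout differs by arm, which is plausible because patients are not blinded and one arm receives no acupuncture during the study; the article gives no figures by arm. The direction of that bias is not determined. The relapse size, dropout timing, dropout splits and correlation used here are all assumptions.

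**What to change.** For both comparisons, name a likelihood-based mixed model for repeated measures that includes all randomised patients, uses every available visit and keeps arms as randomised. State that it is valid under missing-at-random.

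Replace LOCF with a sensitivity analysis that can contradict persistence: multiple imputation of missing follow-up scores with a delta shift, or towards the wait-list or baseline. This second part is needed because the mixed model does not remove bias when dropout depends on the unseen score (3.18 against 4.02 above).

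The cost is a change of wording and a slightly more complex sensitivity analysis. No extra patients or visits are required.
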